**Controlling behavior**: couples will be asked six questions: (i) “jealous if she talked with other men”, (ii) ”accused her of unfaithfulness”, (iii) “did not permit her to meet her friends,(iv) “tried to limit her contact with family,(v) “insisted on knowing where she is, and “did not trust her with money(Antai, 2011). Couples responded “yes” to one or more of the control questions coded as 1. Otherwise, it will be coded 'no as 0.

**Women’s autonomy**: women's decision-making Autonomy will be assessed by asking couples who decide on household purchases, including small and large ones, and who decides on visiting relatives and friends. Who decides how to spend the wife's earnings? Who decides the number of children to have? And who decides to obtain health care for themselves? The response options will be “husband only’’, wife only’’ or ‘’both husband and wife”. Women will be considered to participate in decision-making if they make decisions alone or jointly with their husbands. A composite measure will be created using the sums of equally weighted binary input variables. Women will be scored one (1) for answers to each variable that included her (alone or jointly) in decision-making; otherwise, they will be scored zero (0). The index of household decision-making power (autonomy) contains five variables; thus, the respondents will be scored from 0 to 5. Two binary measures from these indexes will be created to indicate women with higher versus lower autonomy. The high and low categories will be created by dividing the sample indexes into approximately half, in which those who score below the mean score are considered to have low autonomy or lower involvement in household decision-making, and those who score above the mean score are considered to have higher decision-making autonomy or higher involvement in household decision-making (Uthman et al., 2009).

**Women’s Self-Efficacy: The** Generalized Self-Efficacy Scale (GSES), which was developed by Albert Bandura, will be used. The General Self-Efficiency Scale (GSES) consists of 10 items scored on a 4-point Likert scale, from 1 (not at all true) to 4 (exactly true). The total scale ranges from 10 to 40, with higher self-efficacy (score of ≥20) and lower self-efficacy (score of <20) (Liping Peng et al., 2020).

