| 700 | **SELF-EFFICACY**  This questionnaire is a series of statements about your personal attitudes and traits.  Each statement represents a commonly held belief. Read each statement and decide to what  extent it describes you. There are no right or wrong answers. You will probably agree with some  of the statements and disagree with others, Please indicate your own personal beliefs about each  statement below by marking the letter that best describes your attitude or feeling. Please be  truthful and describe yourself as you really are, not as you would like to be.  This questionnaire is a series of statements about your personal attitudes and traits.  Each statement represents a commonly held belief. Read each statement and decide to what  extent it describes you. There are no right or wrong answers. You will probably agree with some  of the statements and disagree with others, Please indicate your own personal beliefs about each  statement below by marking the letter that best describes your attitude or feeling. Please be  truthful and describe yourself as you really are, not as you would like to be.  This questionnaire is a series of statements about your personal attitudes and traits. Please indicate your own personal beliefs about each statement when the interviewer reads that best describes your attitude or feeling   1. Not at all true 2. Hardly true 3. Moderately true 4. Exactly true | | | | | | Encircle the choice | | | | | | | | | | | | |  | | |
| 701 | I can always manage to solve difficult problems if I try hard enough | | | | | | 1 | | | | 2 | | | | 3 | | | | 4 |  | | |
| 702 | If someone opposes me, I can find the means and ways to get what I want. | | | | | | 1 | | | | 2 | | | | 3 | | | | 4 |  | | |
| 703 | It is easy for me to stick to my aims and accomplish my goals. | | | | | | 1 | | | | 2 | | | | 3 | | | | 4 |  | | |
| 704 | I am confident that I could deal efficiently with unexpected events | | | | | | 1 | | | | 2 | | | | 3 | | | | 4 |  | | |
| 705 | Thanks to my resourcefulness, I know how to handle unforeseen situations | | | | | | 1 | | | | 2 | | | | 3 | | | | 4 |  | | |
| 706 | I can solve most problems if I invest the necessary effort. | | | | | | 1 | | | | 2 | | | | 3 | | | | 4 |  | | |
| 707 | I can remain calm when facing difficulties because I can rely on my coping abilities | | | | | | 1 | | | | 2 | | | | 3 | | | | 4 |  | | |

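### Autonomy is cut at a sample mean whose wave and arm are not fixed, and self-efficacy at 20 on a 10–40 scale: before–after autonomy shares may not be comparable and the self-efficacy cut costs power; objective 5 should rest on the scores

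*Protocol*

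**What the plan says.** Autonomy, section 6.17: the index "contains five variables; thus, the respondents will be scored from 0 to 5". Then "The high and low categories will be created by dividing the sample indexes into approximately half": "those who score below the mean score are considered to have low autonomy", and "those who score above the mean score are considered to have higher decision-making autonomy". No numerical cut is given. The text does not name the survey round that supplies the mean, does not say whether the arms are pooled, and does not place a score equal to the mean.

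Self-efficacy, section 6.17: the scale "consists of 10 items scored on a 4-point Likert scale, from 1 (not at all true) to 4 (exactly true"), and "The total scale ranges from 10 to 40, with higher self-efficacy (score of ≥20) and lower self-efficacy (score of <20"). The women's questionnaire in Annex II codes the upper three answers as "2. Hardly true 3. Moderately true 4. Exactly true".

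Both are secondary outcomes (section 6.6.1) and are the whole of specific objective 5 (section 5.3.2). Section 6.24 plans a McNemar test before against after within each arm for categorical outcomes, a paired t-test within each arm for continuous outcomes, and GEE for the intervention effect. It does not say in which form these two outcomes enter which test.

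**The concern.** A threshold used to measure change must be the same at both measurements. A cut defined by the sample's own mean moves with the data if it is recalculated at endline, and the McNemar comparison then mixes change in the women with change in the yardstick. If it is also recalculated within each arm, each arm is judged against itself and the contrast that objective 5 asks for can largely disappear.

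The self-efficacy cut is fixed, but it sits low. A woman who finds every statement hardly true of herself is already in the higher group. If most women start above 20, only the few below it can register an improvement, and gains higher up the scale are lost.

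**Working it through.** **Ranges as stated.** Self-efficacy: 10 × 1 = 10 and 10 × 4 = 40, which reproduces. Autonomy: five items scored 0 or 1 give 0–5, which reproduces.

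**Where the self-efficacy cut lies.** *Hardly true* is coded 2, and 10 × 2 = 20, so that response pattern is classed as higher. The midpoint is (10 + 40)/2 = 25. Of the 31 possible totals, 21 (20 to 40) are higher. Answers spread evenly at random over the four options would give 94% higher.

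**Effective sample size.** From section 6.8: 216 couples per arm, 20% loss, design effect 1 + 0.05 × (27 − 1) = 2.3. So 216 × 0.8 / 2.3 = 75.1 women per arm. Applying the ICC of 0.05 to these secondary outcomes is an assumption.

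**Power for self-efficacy.** The protocol gives no mean or SD, so both are assumed over a range, with a gain of 0.5 SD in the intervention arm.

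- Score: Φ(0.5 × √(75.1/2) − 1.96) = Φ(3.06 − 1.96) = 86.5%, whatever the mean, with no credit for baseline adjustment.
- Cut at 20: share higher p = 1 − Φ((19.5 − mean)/SD); power = Φ((p1 − p0)/√[(p0(1 − p0) + p1(1 − p1))/75.1] − 1.96).

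| Control mean | Share higher, control → intervention (SD 5; SD 6) | Power with the cut |
|---|---|---|
| 20 | 54.0 → 72.6%; 53.3 → 72.0% | about 67% |
| 22 | 69.1 → 84.1%; 66.2 → 82.0% | 60–62% |
| 25 | 86.4 → 94.5%; 82.0 → 92.2% | 40–47% |
| 28 | 95.5 → 98.6%; 92.2 → 97.2% | 20–29% |
| 30 | 98.2 → 99.5%; 96.0 → 98.8% | 12–19% |

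Using the pooled variance under the null lowers these by at most about one point.

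**Autonomy under each reading.** Illustration: beta-binomial scores on 0–5 (item probability 0.5 or 0.7, shape parameters summing to 3). Both arms have mean 2.5 at baseline; at endline control stays at 2.5 and intervention reaches 3.5. High means strictly above the cut.

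| Cut used at endline | Control high | Intervention high |
|---|---|---|
| Baseline mean, 2.5 | 50% | 75.4% |
| Pooled endline mean, 3.0 | 30.5% | 57.3% |
| Each arm's own endline mean, 2.5 and 3.5 | 50% | 57.3% |

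Second row: power for the arm difference at 75 per arm is about 92%, so the arms do separate. But the control arm, at 50% at baseline, appears to fall by 19.5 points although nothing changed. With 216 × 0.8 = 173 control women and no individual score changing, 0.195 × 173 ≈ 34 women move from high to low and none the other way. The McNemar statistic is 34²/34 = 34, a highly significant decline that did not happen.

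Third row: a one-point gain is left as a 7-point difference (3 points with a plain binomial model: 52.8% v 50%).

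The index takes whole numbers, so the moving cut acts in jumps. A pooled endline mean just under 3 gives 50% v 75.4%; at or just above 3 it gives 30.5% v 57.3%. With a smaller gain (intervention mean 3.0, pooled mean 2.75), control stays at 50% and intervention is 63.1%. A within-arm cut is equally erratic: means of 3.0 and 3.75 leave 43% v 65%.

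**The case against.** A reader might infer that neither outcome can show an effect. The documents do not support that. Section 6.17 speaks of the sample and never says that the autonomy cut is set by arm or recomputed at endline. A baseline cut carried forward fits the text as well, and both that and a pooled endline cut separate the arms in the illustration. The self-efficacy cut loses power, but not all of it.

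A reader might also infer that nearly everyone will be classed as higher on self-efficacy. That depends on a distribution the protocol does not give: with SD 4–7 the share is 53–55% at mean 20, 64–73% at 22, 78–92% at 25 and 93–99.6% at 30. Nor does it help to set the headroom above 92% against a detectable difference of about 12 points. That figure uses the variance at 92% in both arms and would take the second arm past 100%.

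Nor does it follow that a real improvement would be reported as none. Section 6.24 has a paired t-test for continuous outcomes, and section 6.6.1 gives binary codings for knowledge, attitude and controlling behavior but none for these two, so analysis of the totals is not excluded. This stands in part: the t-test names no outcome and works within each arm, so it does not compare the arms.

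Finally, both cuts are cited to published work that cannot be read here, so 20 may be an established threshold, and a cut below the midpoint is not in itself an error. The gap at a score equal to the mean is minor, because the mean of several hundred whole numbers is seldom a whole number. Reference wave and pooling could be settled in an analysis plan. But the protocol has already chosen a sample-dependent cut, which is why the point is more than missing detail.

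**Conclusion.** The point holds in a limited form. The autonomy cut is data-dependent and its reference sample is not fixed. If it is recomputed at endline, before–after shares are not comparable, an unchanged control arm can appear to decline in the planned McNemar test, and a cut set within each arm can nearly remove the contrast. How far depends on where the means fall relative to whole numbers; the figures come from an assumed score distribution.

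The self-efficacy cut is arithmetically equal to *hardly true* throughout, and it loses power at every mean examined: from about 86% on the score to about 67% at mean 20 and 12–19% at mean 30. This assumes a 0.5 SD gain, SD 5–6, normal scores and about 75 effective women per arm. Only the position of the cut is a fact from the document; the size of any ceiling is not known. Both are secondary outcomes, so the primary comparison is untouched. The change is worth making because it is free.

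**What to change.** In sections 6.17 and 6.24, state for objective 5 that the main analysis is the between-arm difference at endline in the autonomy total (0–5) and the self-efficacy total (10–40), adjusted for the baseline score and for kebele clustering.

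If high/low displays are kept:

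- Autonomy: fix one cut from the pooled baseline of both arms, say where a score equal to it goes, and apply it unchanged at endline.
- Self-efficacy: justify the cut of 20 or drop it.

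The cost is wording only. Both totals are built from items already collected at both surveys; no extra data, visits or participants are needed.

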**6.18 Data Collectors**

**Data collectors for quantitative study:** 10 diploma-level female nurses will be selected to collect data from the respondents as recommended by WHO to enhance the disclosure of IPVp (WHO, 2007). Data collectors will be trained by the researcher for three days. The selection criteria include:

- Certified diploma female nurses
- Able to fluently speak Amharic and the local language (Hadiyisa).
- Having good interpersonal and communication skills.
- Willing to collect data at the baseline and end of the study

**Data collectors for the qualitative study**: two female moderators will be selected to facilitate FGD. The moderators will be female master’s holders in public health, and those with previous experience in qualitative data collection will be recruited. The same number and criteria as the FGD moderators will be used for the in-depth interview (IDI). The recruitment for the FGD moderators and IDI (interviewers) includes the following criteria: having a master’s degree in the area of public health, being able to speak Amharic and local languages (Hadiyisa), and having previous experience in qualitative data collection.

**Supervisors for quantitative study**: Two supervisors will be recruited for quantitative data collection. When recruiting the supervisor, a master’s degree in a related field and, preferably, previous supervision experience will be used. Their role in the field includes: monitoring health educators and data collectors; making sure education is properly implemented; helping educators and data collectors with any challenges faced during field work; and informing the researcher of any concerns.

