**6.6 Study variables**

**6.6.1 Dependent variables**

**Primary outcome variable**

- Intimate Partner Violence (experience versus not experiencing IPV)

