## 6.13 Blinding

Neither the Health extension workers nor the participants will be informed about the intervention hypothesis

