**6.15.3 Intervention fidelity**

Intervention fidelity refers to the degree to which components of intervention are executed as designed. To enhance the intervention's fidelity, we will implement the following actions: a trainer manual has already developed; extensive training will be provided for interventionists (HEWs); spot checks will be conducted by field supervisors during each intervention session; and feedback meetings with interventionists will be held after each session. A fidelity checklist that addresses adherence and intensity of the intervention will be used to evaluate intervention fidelity at the end of each session.

Table 2:summary of the intervention package and implementation process

| **Session** | **Content of the message** | **Dose** | **Strategy of delivery** | **Frequency** | **Compliance parameters** | **Responsible person** |
| --- | --- | --- | --- | --- | --- | --- |
| Session 1  (13-16 weeks) | - Introducing each other - Gender based violence (what is it) - Violence against women(what is it) - Intimate partner violence(what is it ) - Types of intimate partner violence - Physical, sexual and psychological - Magnitude of IPV - Summarization - Introduction on take home-exercise next - Appointment to next session | 60 minutes | • Brain storming • Lecture • Question and Answer  **.**Take-home exercise and reflections | Once | -% couples participated | Researcher, Supervisors & Health extension workers |
| Session 2  (17-20 weeks) | - Refelection on take home exercise and recap - Maternal and new born consequences of IPV - Economic and social consequences - Family and dependents consequences - Common triggers of IPV during pregnancy - Ways to challenge triggers of IPV - Introduction on take-home exercise - appointment to next session | 60 minutes | • Brain storming • Lecture • Question and Answer  **.**Take-home exercise and reflections | Once | -% -% couples participated | Researcher, Supervisors & Health extension workers |
| Session 3  21-24 weeks | - Reflection on take home exercise - Common gender norms for women and men - Gender and sex - Inequality gender norms related to IPV during pregnancy - The ways to challenge inequitable gender norms - Introduction on take-home exercise and appointment to next session | 60 minutes | • Brain storming • Lecture • Question and Answer  **.**Take-home exercise and reflections | Once | -% -% couples participated | Researcher, Supervisors & Health extension workers |

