**6.21 Data collection instruments**

**Questionnaires**

**Quantitative study**: structured-interviewer-administered questionnaires adapted from the WHO multi-country study questionnaire will be used to collect information on intimate partner violence in pregnancy (WHO, 2010). The English version of the questionnaire will be translated into the local language (Hadiyisa) by fluent speakers. Then, the questionnaire's local language will be translated back to English by another expert to ensure consistency and accuracy. Four types of questionnaires will be administered at baseline and at the endline for couples (pregnant wife and husband). The data will be collected using a mobile-based application called KoBo Collect. The content of the information under each questionnaire will be as follows:

**Questionnaire for pregnant mothers at baseline and end-line**: the questionnaire will be administered to all pregnant women in the two groups (intervention and control groups) after obtaining informed verbal and written consent. The questionnaire contains individual characteristics of mothers, including age, levels of education, occupation, marriage type, parity, pregnancy intention, and household characteristics. Relational characteristics: duration of marriage and disparity in educational attainment

Moreover, the relational characteristics include the presence of social support and religion. The societal characteristics of pregnant women include women’s autonomy in addition to male involvement in antenatal care. All questionnaires will be administered to the intervention and control groups before any education session. Outcome measures: couples' knowledge, attitude, and control towards IPV; self-efficacy; pregnant women’s experience of IPV in the last 12 months and during the recent pregnancy

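### The protocol does not keep outcome interviewers unaware of kebele allocation, and it links education delivery to outcome collection through shared supervisors and a work-plan row that lists educators at baseline

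*Protocol*

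**What the plan says.** **Outcome.** Protocol 6.6.1 makes experience of intimate partner violence, yes or no, the primary outcome. Under 6.17, one positive answer to a physical, sexual or psychological item makes the woman a case for that type; 5.10 counts any type as partner violence. Section 6.21 collects this with "structured-interviewer-administered questionnaires adapted from the WHO multi-country study questionnaire".

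**Interviewers.** Section 6.18 states that "10 diploma-level female nurses will be selected to collect data from the respondents". One selection criterion is "Willing to collect data at the baseline and end of the study", so the same people are intended at both surveys. Section 6.19 trains them on the study aim and objectives; objective 4 in 5.3.2 is the effect of the education on experience of violence.

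**Blinding.** The whole of 6.13 reads: "Neither the Health extension workers nor the participants will be informed about the intervention hypothesis". Section 6.15.2 repeats it. Section 6.12 adds that the randomising statistician is blind to the study groups. No section mentions interviewers.

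**Supervisors.** Section 6.18 describes their field role as "monitoring health educators and data collectors" and "making sure education is properly implemented". Section 6.15.3 adds that "spot checks will be conducted by field supervisors during each intervention session". Section 6.23 has supervisors check the collected data daily. Table 2 lists supervisors for every session and for endline data collection.

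**Educators.** Table 4 (section 7) lists researcher, supervisors, educators (Ed) and data collectors as responsible for baseline data collection. It lists the same four for a row whose label runs intervention and data collection together. Table 2 lists researcher, supervisors and data collectors for endline, without educators.

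**The concern.** Violence is a sensitive subject, and what a woman discloses can depend on who asks and how the interviewer probes. The protocol accepts this when it chooses female nurses in order to raise disclosure (6.18). If interviewers know which kebeles were trained, or take direction from people accountable for the training, probing and recording may differ between arms. The analysis in 6.24 (McNemar, paired t-test, GEE) cannot distinguish a difference in reporting from a difference in violence.

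Baseline matters too, because the before–after comparisons use it. Section 6.15 draws the eight educators from the intervention kebeles, so educators as a staff group exist in one arm only. Any part they play in baseline collection would, by inference, fall in that arm.

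**Working it through.** **1. Who knows allocation, and when.** Section 6.12 randomises clusters before participants are recruited, and Figure 5 shows the same order, with baseline data collection after allocation. The column headings of Table 3 put enrolment before allocation, but the text of 6.12 is explicit. Allocation therefore exists when the baseline interviews take place. Supervisors know it from attending sessions. For interviewers the protocol is silent: it neither says that they are told nor provides that they are not.

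**2. Who collects the data.**

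| Source | Baseline | Endline |
|---|---|---|
| 6.18 | ten nurses | the same ten nurses |
| Table 2 | not covered | researcher, supervisors, data collectors |
| Table 4 | researcher, supervisors, educators, data collectors | no separate row |

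The conflict is clear at baseline. At endline the only specific source, Table 2, leaves educators out. The combined row of Table 4 is ambiguous: it is also the only row covering delivery of the education, where educators belong.

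**3. The planned effect, as a yardstick.** Inputs from 6.8: 37.5% prevalence, a 20% decline, 80% power, design effect 1 + 0.05 × (27 − 1) = 2.3, and 20% loss. Two-sided 5% is from 6.24.
- Read as 20 percentage points (37.5% to 17.5%), the pooled two-proportion formula without continuity correction gives 78 per arm. Then 78 × 2.3 = 179.4, rounded up to 180, and 180 × 1.20 = 216, the stated figure.
- Read as a relative decline (37.5% to 30%), it gives 623 per arm. Then 623 × 2.3 = 1,432.9, rounded up to 1,433, and 1,433 × 1.20 = 1,720 after rounding up. This does not reproduce 216.

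**4. Illustration of size.** The documents give no figure for reporting bias, so the extra non-disclosure r is an assumption. Suppose there is no true effect, prevalence is 37.5% in both arms, and r applies to the intervention arm. The observed prevalence there is 0.375 × (1 − r), and the spurious difference is 0.375 × r. With 20% attrition there are 216 × 0.8 = 172.8 couples per arm and 21.6 per cluster. The design effect is then 1 + 0.05 × 20.6 = 2.03, and the effective size is 172.8 / 2.03 ≈ 85 per arm. The last column is the chance that a two-sided 5% test rejects (normal approximation).

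| r (assumed) | Observed | Spurious difference | Share of 20 points | P(reject) |
|---|---|---|---|---|
| 5% | 35.6% | 1.9 points | 9% | 0.06 |
| 10% | 33.8% | 3.8 points | 19% | 0.08 |
| 20% | 30.0% | 7.5 points | 38% | 0.18 |
| 30% | 26.3% | 11.3 points | 56% | 0.35 |

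If disclosure were lower in the control arm instead, the differences would have the same size and the opposite sign.

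**The case against.** The strongest reply is that safeguards exist and the link to the outcome is indirect. Interviews are private, at a place and time the respondent chooses (6.24 Ethical Consideration). Ten nurses, not the educators, are named as interviewers. Supervisors do not interview, and the checks described in 6.23 concern completeness, consistency, survey duration and GPS points. Baseline questionnaires precede any education session (6.21), so no woman has yet been taught by an educator at that point. Women who attended six sessions know it, and their own wish to please survives any rostering.

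All of this stands, and it limits the point. It does not supply a masking provision for interviewers, nor does it reconcile Table 4 with 6.18.

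A reader might infer more than the documents support:
- **That educators sit in on interviews or collect endline data.** No section says so. The privacy rule points the other way, Table 2 omits educators at endline, and being listed as responsible is not the same as interviewing.
- **That interviewers are told the allocation.** The protocol is silent on this.
- **That the bias favours the intervention.** Sessions that teach what counts as violence could raise recognition and reporting in the intervention arm and so hide a benefit.

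**Conclusion.** The point holds as a weakness in conduct that is cheap to repair. For a subjective, interviewer-recorded primary outcome, the blinding section leaves out the people who record it, the same supervisory role covers delivery and data collection, and Table 4 contradicts 6.18 on who collects baseline data. The result is a risk of differential measurement by arm, of unknown size and direction.

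The 3.8–7.5 points rest entirely on an assumed 10–20% difference in disclosure. That is 19–38% of the 20-point fall behind the stated 216 per arm, with false rejection of about 0.08–0.18 in place of 0.05. It would be tempting to say that 7.5 points equals the whole planned effect. That is true only if the 20% decline is relative, a reading the stated sample size does not support. Nor should the whole assumed difference be charged to staffing, since part of any reporting bias would come from the women themselves.

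**What to change.** - **6.13 and 6.18:** state that the nurse interviewers are not told kebele allocation and are rostered across both arms at baseline and endline.
- **Table 4, baseline data collection:** remove Ed.
- **Table 4, combined intervention and data-collection row:** split it so that educators appear only under delivery of the education, consistent with 6.18 and Table 2. Deleting Ed from the row as it stands would remove educators from the only row that covers the intervention.
- **Endline supervision:** where feasible, have each supervisor oversee interviews only in kebeles where they did not spot-check sessions. The other changes stand even if this proves impractical.

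The cost is wording and rostering, perhaps with some extra travel. No staff are added and the sample size does not change. The limit is that masking will be partial: women may mention the sessions, and supervisors will still know the allocation even when crossed.
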